**Background**

Difficulty with walking represents the first stage of decline in physical function, as it is typically the first activity limitation that older adults develop. “Serious difficulty walking or climbing stairs”, referred to as “mobility disability” leads to larger declines in quality of life than depression, anxiety, or pain and to significant increases in financial stress. Older adults with mobility disability are 8.7 times more likely to die, incur an additional $10,000 each year in health care costs and are 13-36 times more likely to transition to a nursing home in the near future.

Resistance training (RT) improves mobility disability but too few older adults do it. Systematic reviews observe that 6 months of RT increases strength by 50% in older adults, which improves mobility (Cohen’s d=0.61, 5 trials). Despite these identified benefits, fewer than 20% of older adults meet national guidelines for doing RT twice per week. There is a clear need to create RT options for older adults that improve physical function and that most are willing to do.

Our team has observed that 84% of older adults with difficulty walking preferred doing RT 5 minutes per day versus the traditional 45 minutes three-times weekly in part due to physical limitations and pain. Briefer RT sessions are also supported by evidence that aerobic exercise high-intensity interval training leads to large increases in fitness in as little as 3 minutes per week, while systematic reviews observe that most of the strength gains are from the first few sets each week. These prior studies suggest that longer programs that include RT may not always be necessary for health benefits and might discourage participation among people with mobility challenges.

Our goal, is to design a brief RT program that can improve physical function among older adults. We have designed a program called FAST (Functional Activity Strength Training) augmented with goal-setting, rarely used in RT studies, for the number of additional repetitions participants should be able to do over time. Our first study in 24 healthy older adults (FAST-1) included prescribing 30 seconds of squats and push-ups each day with given no personal supervision. Over six months, participants performed the exercises on 73% of days and showed large increases in squat performance (+6.2 repetitions, Cohen’s d > 1.0). This study lacked a control group and evaluated only self-reported outcomes. In the current study (FAST-2), we build on this study to test whether FAST can, in 4 minutes of RT per day, improve physical function among older adults with mobility disability

**Study Hypothesis**

We hypothesize that participants randomized to the FAST-2 treatment intervention will improve measures of lower extremity performance that are strongly associated with future disability, in 12 weeks, compared to those randomized to the delayed treatment control.

**Primary Study Endpoints**

| **Measure** | **Timing** |
| --- | --- |
| Five-Times Sit-to-Stand (FTSTS) test | Baseline, week 6 and week 12 |
| One-Legged Stance Test (OLST) | Baseline, week 6 and week 12 |
| 30 second chair test | Baseline, week 6 and week 12 |
| Exercise daily performance | Daily for 12 weeks |

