**Intervention**

FAST-2 will be a two-group, 12-week, delayed-treatment randomized trial.

Participants will be provided with a set of four resistance bands with handles (10-40 pounds of resistance) and a standard aerobics stepper that can be adjusted to 4, 6, or 8 inches in height prior to the baseline visit. They will be instructed to perform four exercises daily, each lasting 30 seconds, and to perform as many repetitions as possible during those 30 seconds. Thirty seconds of rest will be allowed in between the exercises. Each day participants will be asked to perform push-ups, chair stands, two-arm rows, and stair stepping in the same order during each session. No written instructions will be provided, although links to videos of each exercise will be included in email communications. Participants will be instructed to perform the exercises all seven days of the week. Modifications will be provided based on the participants’ functional level and form.

Push-ups can be modified in any of the following ways: by resting on the knees instead of the toes, by placing the hands on the kitchen countertop (30 inches in most homes), by placing the hands on a set of steps (starting with the 4^th^ step from the floor) or by placing the hands on the wall. When participants are able to perform 15 repetitions of push-ups using one of the modified methods, they will beasked to progress to a higher level of difficulty (e.g., place the hands on the 3^rd^ step from the floor).

Chair stands will be performed, by default, by placing the arms across the chest, but participants can modify them if needed by placing two hands on the knees, one hand on a knee or with arms not placed across the chest. Participants will be instructed to use a standard chair with arms, without wheels and with a seat height of approximately 17 inches regardless of the height of the subject. Participants will be encouraged to progress, as they are able to do so safely, to the default position of placing their arms across the chest.

Two-arm seated band rows will be performed with the resistance band looped around the arches of the feet to allow for a full range of motion. Participants will be instructed to pull their elbows back to touch the body to complete a repetition while squeezing the shoulder blades behind together.

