Participants will complete the stair stepping exercise by placing their feet up on the step reciprocally and then stepping backwards down in the same fashion. All participants will start on the 4-inch step until they can rise fully on the step with both feet six times in 30 seconds. They will be then instructed to increase the step height to 6 inches and later to 8 inches.

To increase safety, participants will be instructed to place the chair on carpet or against a sturdy object like a wall. For the stair stepping exercise, participants will be instructed to place the stair stepper in the corner of a room, so they can touch the wall if they feel unsteady.

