## Delayed intervention control

Participants assigned to the delayed intervention control group will continue care as usual. Following the completion of the 12-week follow-up, participants in the delayed group will begin 12 weeks of physical activity intervention with a one-on-one audio-video Zoom coaching session occurring during the initial first week. At that time, the information given to the physical activity treatment intervention group regarding the daily exercise will be given to the delayed group.

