## Statistical analysis

Summary statistics (e.g., mean and standard deviation (SD) for continuous variables; frequency and proportion for categorical variables) will be reported for participant baseline characteristics. Baseline differences between randomly assigned participants will be evaluated with two-sample t-tests and Fisher’s exact tests. Changes in the primary outcome measures over 12 weeks will be evaluated at the group level using linear mixed-effect models to analyze change over time and the Group x Time interaction. The analysis will employ an intention-to-treat approach, with missing data addressed through mixed-effects modeling in the longitudinal data analysis framework. A two-sided *p*-value of less than or equal to .05 will be considered statistically significant.

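### Daily exercise performance is a listed primary endpoint, but controls have no such data in the 12 weeks, so the planned Group x Time test cannot be estimated for it

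*Protocol*

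**What the plan says.** The Protocol's Primary Study Endpoints table has four rows. Three are functional tests at baseline, week 6 and week 12. The fourth reads "Exercise daily performance | Daily for 12 weeks". The Measures section is consistent with this: daily exercise performance is described under Primary Outcome Measures, ahead of the secondary outcome, as repetition counts for four exercises that participants enter in a daily survey.

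The Statistical analysis section states that "Changes in the primary outcome measures over 12 weeks will be evaluated at the group level using linear mixed-effect models", and gives the purpose as "to analyze change over time and the Group x Time interaction". It exempts no primary outcome. The Study Hypothesis is comparative, stating that the active arm "will improve measures of lower extremity performance that are strongly associated with future disability, in 12 weeks, compared to those randomized to the delayed treatment".

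On the control arm, the Delayed intervention control section says "Participants assigned to the delayed intervention control group will continue care as usual". It continues: "Following the completion of the 12-week follow-up, participants in the delayed group will begin 12 weeks of physical activity intervention", and the daily exercise information is given to them at that point. The Functional Performance Measures section has both groups complete the three functional tests; the daily log is not among them.

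**The concern.** A Group x Time interaction compares the time course in one arm with that in the other. An outcome that exists only for people doing the programme has no control time course to compare with. As written, one of the four declared primary endpoints cannot be given the test assigned to it and cannot address the between-group hypothesis.

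If the endpoint stays on the primary list, the only result available for it is a before-after change in the treated arm. Reported as a primary outcome of a randomised trial, that change would look like randomised evidence when it is not. It would also bring back, for this endpoint, the two limits that the Protocol's own background names for the pilot: no control group and self-reported outcomes.

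**Working it through.** **The Protocol's own sample size.** Inputs from Sample size determination: d = 0.60, two-sided alpha 0.05, power 80%, attrition 20%.

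- n per group = 2 × (1.960 + 0.842)² / 0.60² = 43.6, rounded up to 44; total 88. Power at 44 per group is 0.804 by the normal approximation. The exact t-test gives 0.795 at 44 per group, or 45 per group for 80%, which is a negligible difference.
- Recruitment: 88 / (1 − 0.20) = 110.

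Both stated figures reproduce. They apply to an outcome measured in both arms.

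**Who supplies data in weeks 1 to 12.**

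| Primary endpoint | Intervention | Control |
| --- | --- | --- |
| Five-Times Sit-to-Stand | yes | yes |
| One-Legged Stance | yes | yes |
| 30-second chair stand | yes | yes |
| Daily exercise performance | yes | no (programme starts after week 12) |

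**What the model can estimate.** Take the simplest form of the planned model, with G = 1 for intervention and 0 for control, and t for time:

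mean = b0 + b1·G + b2·t + b3·G·t

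With daily data over 12 weeks (84 days):

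- Intervention arm only: every row is (1, 1, t, t). Columns 1 and 2 are identical, and so are columns 3 and 4. The rank is 2 of 4. Only the sums b0 + b1 and b2 + b3 are identified. The group effect b1 and the interaction b3 are not.
- Both arms: control rows (1, 0, t, 0) are added and the rank becomes 4 of 4.

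This does not depend on n, so 88 participants give no power for the interaction on this endpoint. The plan to handle missing data through the mixed model does not help either, because the outcome is absent by design for a whole arm. Control counts collected after week 12 would not be concurrent and would come from participants who are then receiving the programme.

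**What the within-arm trend would measure.**

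- Push-ups: a harder level is asked for "When participants are able to perform 15 repetitions of push-ups using one of the modified methods".
- Stair stepping: "All participants will start on the 4-inch step until they can rise fully on the step with both feet six times in 30 seconds"; the step is then raised to 6 inches and later to 8, with no stated count for the second change.
- Chair stands: participants who modify the exercise are encouraged towards arms across the chest, with no count trigger.
- Rows: no progression rule is stated.

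For three of the four exercises, then, the task being counted can change during follow-up. The Protocol gives no rule for combining counts across exercises or difficulty levels. Two of the four exercises, push-ups and rows, are not lower-extremity measures, whereas the hypothesis concerns lower-extremity performance.

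**The case against.** Five points can be made on the other side.

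- **The stated analysis covers change over time as well as the interaction.** This stands. A time trend in the intervention arm is estimable, so a reader who infers that the endpoint cannot be analysed at all goes too far. The trend is not, however, a comparison with control, which is what the hypothesis requires.
- **The progression rules do not spoil the counts.** This stands in part. A reader might infer that progression resets the counts, or caps push-ups at about 15. The Protocol says neither. A repetition trigger is given only for modified push-ups and for leaving the 4-inch step, and participants are asked or encouraged to move on. The Protocol also uses counts as coaching goals (four more chair stands and two more steps over 12 weeks). What survives is that difficulty is not constant, so a count can understate improvement; the documents give no figure for how often or by how much.
- **Blinded coders review videos weekly and settle disagreements over repetitions.** This is true and belongs in a fair description. The text ties that adjudication to sessions conducted by research staff and does not say that each daily survey entry is verified. Mainly self-reported is therefore a fair description.
- **A SAP that is not shown may deal with it.** It may reclassify the measure. The Protocol's own classification and its own analysis statement would still conflict with its design.
- **The main comparison is intact.** This stands in full. The three functional tests are done in both groups, and the sample size rests on physical function.

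**Conclusion.** The point holds as a contradiction within the Protocol. One of four primary endpoints is assigned a between-group test for which the control arm supplies no data in weeks 1 to 12, so its group and Group x Time effects cannot be estimated at any sample size. The most it can yield is an uncontrolled, mainly self-reported time trend in the intervention arm, recorded while exercise difficulty changes, with two of its four components outside the hypothesis.

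This rests on reading the daily survey as part of the programme. The Protocol supports that reading: the survey link comes with the daily workout reminder, and controls get the exercise information only after the 12-week follow-up.

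A reader might go further and infer that the trial's randomised test is compromised or that the sample size must change. The documents do not support that: the other three primary endpoints are measured in both arms, and 88 and 110 both reproduce.

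**What to change.** - Remove daily exercise performance from the Primary Study Endpoints table and from the Primary Outcome Measures part of the Measures section.
- Describe it as a process measure, reported descriptively for the intervention arm only and split by whether modifications were used. That is the field the survey is said to record. Reporting by step height, push-up version or arm position should not be promised, because the Protocol does not say that these are logged.
- In Statistical analysis, name the Five-Times Sit-to-Stand test, the One-Legged Stance Test and the 30-second chair stand as the outcomes for the Group x Time model.

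The cost is Protocol wording. Data collection, sample size and the other three endpoints stay as they are; the only loss is that the trial declares three primary endpoints instead of four.

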## Secondary Study Endpoints

| **Measure** | **Timing** |
| --- | --- |
| Adherence reporting | Daily |

#

**Ethics Approval and Informed Consent**

Study protocols were reviewed and approved by the Penn State University Institutional Review Board (IRB # STUDY00016054). Written informed consent will be obtained from all participants. All research will be conducted in accordance with the Declaration of Helsinki, Good Clinical Practice guidelines and Penn State Health local regulatory requirements. The study will followthe Consolidated Standards of Reporting Trials (CONSORT) reporting guideline and has been registered at [www.clinicaltrials.gov](https://www.clinicaltrials.gov/) under the identification number NCT05697497.

**Methods**

**Participants**

Eligible participants will be identified through mailing recruitment letters to Penn State Health patients ≥ 65 years of age meeting eligibility criteria and residing in zip codes within a 30-mile radius of Penn State Health-Milton S. Hershey Medical Center.

Eligibility screening process

Screening for eligibility will occur prior to the signing of the informed consent document. Interested participants will be screened by phone by research staff who will read a phone screening document which will ensure eligibility and inform them of study procedures.

During screening, the items from the Physical Activity Readiness Questionnaire (PAR-Q; attached) will be asked. The participant answers will be transferred to the permission slip (attached) by research staff and will be faxed to the Primary Care Provider (PCP) of the participant for the PCP to review and provide permission.

**Inclusion and Exclusion Criteria**

**Inclusion Criteria**

1. Age 65 and older
2. Difficulty with walking
3. Providers must provide consent for their patient
4. Access to the internet
5. Must have a camera on computer, tablet, or smartphone
6. Fluent in English

**Exclusion Criteria**

1. Chest pain or a heart condition on the PAR-Q
2. Planning to have surgery in the next 3 months
3. Cognitive impairment
4. Unable to exercise
5. Being currently physically active

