### Criteria for removal from study

Participants may be from the study if they become injured and cannot exercise or if they are asked by their Primary Care Provider to suspend exercise. The Principal Investigator reserves the right to remove a participant from the study for any reason, based on their discretion, particularly a belief that continued participation exposes them to unnecessary risk. Also, participants have the right to withdraw themselves at any time and halt all study-related activities permanently.

Other withdrawal criteria include: unwillingness to follow protocol during visits, unwillingness to complete study visits, and/or return of equipment to study staff, withdrawal of consent by the participant, development of a new medical problem that would exclude them from the study.

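### Eligibility to exercise is checked only at screening, but the delayed arm starts exercising after week 12 with no re-confirmation stated, and the 3-month surgery window covers at most about 7 of its 84 exercise days

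*Protocol*

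**What the plan says.** **Screening.** The protocol's Participants section (eligibility screening process) describes one phone screen before consent: "During screening, the items from the Physical Activity Readiness Questionnaire (PAR-Q; attached) will be asked". The answers go onto a permission slip that is "faxed to the Primary Care Provider (PCP) of the participant for the PCP to review and provide permission". Inclusion Criteria makes the provider's consent a condition of entry.

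**Exclusions.** Exclusion Criteria lists "Chest pain or a heart condition on the PAR-Q" and "Planning to have surgery in the next 3 months". Only the surgery item carries a time limit.

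**Delayed arm.** Delayed intervention control says: "Following the completion of the 12-week follow-up, participants in the delayed group will begin 12 weeks of physical activity intervention". At that point it mentions a "one-on-one audio-video Zoom coaching session occurring during the initial first week" and handing over the exercise information. It mentions no repeat of the PAR-Q, the surgery question or the PCP permission.

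**Removal.** Criteria for removal from study allows removal of participants "if they become injured and cannot exercise or if they are asked by their Primary Care Provider to suspend exercise", or at the Principal Investigator's discretion. It also lists "development of a new medical problem that would exclude them from the study" as a reason for withdrawal. None of these is limited to one arm or one period, and no check is scheduled to find such cases.

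**The concern.** For participants in the immediate arm, the screening questions come shortly before exercise begins. For those in the delayed arm, the same questions are followed by 12 weeks of usual care, and only then by 12 weeks of study exercise. The surgery question therefore looks ahead over weeks in which this arm does no study training, and hardly reaches the weeks in which it does.

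The people concerned are 65 or older, report difficulty walking, and are told to do as many repetitions as possible every day at home. If someone's health or surgical plans change during the control period, the protocol would want to know before training starts: it names a new excluding problem as grounds for withdrawal. As written, it relies on the participant or the PCP volunteering that information. What is at stake is participant safety and a clear eligibility rule for half of those to be trained. The trial's estimate of effect is not at stake.

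**Working it through.** **Inputs**
- Surgery look-ahead: 3 months (Exclusion Criteria) = 3 × 365.25 / 12 = 91.3 days.
- Control period: 12 weeks = 84 days. Delayed-arm exercise: a further 84 days (Delayed intervention control), so days 84 to 168 after baseline at the earliest.
- Lag L from screening to baseline: not stated. Assumed range 0 to 28 days.
- Sample size (Sample size determination): 44 per group, 88 evaluable, 20% attrition, up to 110 recruited.
- Allocation ratio: 1:1 assumed. The sample size section plans equal groups.

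**The plan's own figures.** With d = 0.60, two-sided 0.05 and 80% power, the normal-approximation formula gives n per group = 2 × (1.960 + 0.842)² / 0.60² = 43.6, so 44 per group and 88 in all. Then 88 / (1 − 0.20) = 110. Both figures reproduce.

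**Number affected.** 110 / 2 = 55 at most. Delayed exercise follows completion of the 12-week follow-up, so with 20% attrition about 55 × 0.80 = 44 would reach it.

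**Days of delayed-arm exercise inside the surgery window.** Covered days = max(0, 91.3 − (L + 84)).

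| Lag L (days) | Covered days of 84 | Share |
| --- | --- | --- |
| 0 | 7.3 | 8.7% |
| 7 | 0.3 | 0.4% |
| 14 | 0 | 0% |
| 28 | 0 | 0% |

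Coverage reaches zero at L = 91.3 − 84 = 7.3 days. The protocol does not say from which day the 3 months count. If they count from baseline, the result is the L = 0 row, so about 7 days is the maximum under either reading. Any delay between the week-12 visit and the first workout lowers it further.

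**Age of the other two items.** The PAR-Q answers and PCP permission are at least 84 + L days old when delayed-arm exercise starts, that is, 12 weeks or more. The protocol gives neither a validity period.

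**Could another contact detect a change?**
- In the control period the stated contacts are the week-6 and week-12 performance tests over Zoom (Functional Performance Measures). Their content is the three timed or counted tests.
- The daily survey and the calls after missed sessions concern exercise sessions, which this arm does not yet have.
- The Coaching section lists rapport, review of performance, goals, form and safe set-up. It lists no health question.

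The withdrawal criterion for a new medical problem therefore exists, but no stated contact feeds it.

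**The case against.** Several points on the other side have force.

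**PAR-Q and PCP permission.** A reader might infer that all three clearances have run out before the delayed arm exercises. The documents do not support that. Only the surgery item has a time limit. The permission slip is an attachment that is not shown, and it may ask the PCP to clear the whole programme, including a delayed start. What can be said is that these two items are at least 12 weeks old.

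**Removal criteria.** A reader might also infer that a participant who develops chest pain in the control period would be started on exercise under the plan. That is not so once the problem is known: the removal criteria apply in both arms and throughout. What remains is that nothing stated is designed to make it known.

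**Purpose of the surgery criterion.** No rationale is given. Three months is close to the 12-week randomised period, so the criterion may be there to protect outcome assessment, in which case covering the control weeks is what it is for. This is a fair reading, and the protocol should say so if it is meant.

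**The immediate arm.** It is tempting to add that the window is only about a week longer than the immediate arm's programme and may fall short there too. That rests entirely on the unstated lag and on an assumed starting day for the 3 months, so it is not part of this point.

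**Contact and weight.** Staff do see delayed participants at weeks 6 and 12, and a coaching session falls in the first exercise week. The protocol is silent here; it does not contradict itself outright. These facts lower the weight of the point and also make the remedy easy, because the contact already exists.

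**Conclusion.** The point holds as a gap in the safety process. No re-confirmation of eligibility is stated before the delayed arm begins exercise, and the surgery window covers at most about 7 of that arm's 84 exercise days (8 to 9%). It covers none if the screening-to-baseline lag exceeds about a week. It would be too strong to say that the arm's entire exercise period falls outside the window, since that depends on a lag the protocol does not give.

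Up to 55 participants are concerned, or about 44 after planned attrition. This assumes 1:1 allocation, 3 months of 91.3 days, and delayed exercise starting no earlier than day 84. The randomised comparison over weeks 0 to 12 is not affected, because delayed-arm exercise starts after it ends.

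**What to change.** 1. In Delayed intervention control, state that the protocol's existing PAR-Q items and surgery question are asked again at the existing week-12 contact, before delayed-arm exercise starts.
2. Reconcile the eligibility screening process, Exclusion Criteria, Delayed intervention control and Criteria for removal from study on two questions: which period the surgery criterion is meant to cover, and whether the PCP permission obtained at screening extends to a delayed start. What follows from a changed answer is a clinical rule for the sponsor to decide; none is proposed here.

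The cost is a short amendment and one repeated questionnaire for up to 55 people, using forms that the trial already has. The downside is that a few delayed starts may be postponed or not happen. No analysis changes.
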